This supplement contains the following items:

1. Original study protocol (the version number 1.1 follows internal nummeration. This protocol was approved by the local ethics committee prior to study begin and was not altered thereafter)
2. Original statistical analysis plan (included within the study protocol)

## Rationale and Objectives

In recent years there has been a novel approach for the treatment of chronic pain: Floatation REST (restricted environmental stimulation therapy). Floating is a therapeutic approach developed in the 1950s [6, 7] which patients float in a specialized pool or tank on water that contains high concentrations of Epsom salt (Magnesium sulfate). Water is kept at skin temperature (35-36°C) and the pool or tank is shielded to provide almost complete darkness and silence. This therapeutic approach has proven to be effective in alleviating chronic pain [2].

While the high salinity of the water allows effortless floating and thus leads to muscle relaxation, the dark and silent environment without somatosensory stimulation greatly reduces sensory input. Thus, the two main mechanisms through which floatation REST may influence pain are the floatation itself and the sensory deprivation.

Due to the difficulties associated with designing a credible placebo control there have been no randomized controlled trials (RCTs) with patients blinding so far. Such blinding, however, is crucial, as the futuristic design of the pools / tanks and the unusual form of intervention are prone to elicit large placebo effects.

Here, we plan to conduct the first patient blinded RCT with a credible placebo control for floating and a no-treatment group.

## Study Design

To investigate the therapeutic effects of floating and sensory deprivation on chronic pain we will divide the participants into three groups using a central randomization procedure.

- The **intervention group** will have the full floating experience: high buoyancy and maximal sensory deprivation.
- The **control group** will have a minimal floating experience designed as a placebo control. To achieve this we will manipulate the two mechanisms mentioned above: the water will have reduced buoyancy (low salinity) and there will be visual, auditory and somatosensory stimuli to reduce sensory deprivation to a minimum.
- The **no-treatment group** will be a waiting-list control. Patients in this group will not receive any treatment.

Our study will investigate short- and long-term effects of floating by evaluating separate endpoints after each floating session and after completion of the study (i.e. after five floating sessions).

## Study Category

This study is a monocentric, patient-blinded, randomised and placebo-controlled study.

## Endpoints

The study has **short-term endpoints** to assess the effect of each single floating session and **long-term endpoints** to assess the effect of a course of five successful floating sessions. While the former will be assessed before and after each floating session, the latter will be assessed one week after the final floating session and in two follow-ups at 12 and 24 weeks after completion. The only exception are pain area and widespreadness that will not be included in the follow-up assessments.

The study is successful, when the primary outcome shows significant differences between the intervention group and the control group at first assessment (one week after the final floating session).

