### Primary outcome (long-term):

The primary endpoint of the study is the reduction of pain (maximum and average) as measured by a numeric rating scale (NRS) retrospectively for one week.

**Secondary long-term outcomes** comprise improvements in

- 1.) Reduction of pain (maximum and average) by 30% or more (dichotomous)
- 2.) Pain-related disability (PDI)
- 3.) Trait Anxiety (STAI Trait)
- 4.) Depression (BDI)
- 5.) Quality of life (SF-12)
- 6.) Quality of sleep (NRS)
- 7.) Use of pain medication

**Secondary short-term outcomes** comprise improvements in

- 1.) Acute pain intensity (NRS)
- 2.) Acute pain area and widespreadness (from electronic pain drawing)
- 3.) State Anxiety (STAI State)
- 4.) Heart rate variability (improvement of sympatho-vagal balance indicated by an increase in HF- and a decrease in LF-HRV)
- 5.) Unusual bodily sensations during floating (electronic drawing)
- 6.) Altered states of consciousness during floating (5D-ASC)

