## Study assessments

- 1.) All pain scores will be acquired using numeric rating scales from 0 ("no pain") to 100 ("maximum imaginable pain"). Ratings will assess the period of one week before the day of assessment.
- 2.) Pain-related disability, state and trait anxiety, depression and quality of life will be assessed using the following validated questionnaires
  - a.) Pain disability index, PDI [9]
  - b.) State-Trait Anxiety Inventory, STAI [10]
  - c.) Beck Depression Inventory, BDI-II [1]
  - d.) 12-Item Short Form Survey, SF-12 [11]

All ratings will assess the period of one week before the day of assessment.

- 3.) Pain area and widespreadness (Widespread pain index, WPI) will be derived from electronic pain drawings acquired using the tablet PC application "SymptomMapper" developed by our group. Ratings will assess the period of four weeks before the day of assessment.
- 4.) HRV will be measured before and after each floating session using a Nilas MV Diagnostik- und Regulationssystem (Nilas MV GmbH, Hamburg).
- 5.) Unusual bodily sensations during floating will be acquired from electronic drawings with the "SymptomMapper" software.
- 6.) Altered states of consciousness will be assessed using the 5-Dimensional Altered States of Consciousness Rating Scale, 5D-ASC [4].
- 7.) Sleep quality will be assessed with a numeric rating scale. Patients will be asked how much their pain impairs their sleep on a scale from 0 ("not at all") to 100 ("very much").
- 8.) Use of pain medication will be assessed by patients' self report.
- 9.) To assess the treatment belief, subjects will receive the following written question "Which treatment do you believe you received?" and offered the replies "real floating", "placebo floating" or "uncertain".

- 10.) To assess credibility of and expectancy in the treatment, a four-item Borkovec and Nau's self-assessment scale will be used [3].

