## Study procedures on each study day

The subject recruitment will start in February 2018 according to the inclusion and exclusion criteria and will be conducted at the Pain Outpatient Department (Schmerzambulanz) of the MHH.

At visit 1 (screening), written informed consent will be obtained. Subjects will undergo a physical examination and medical history taking. In- and exclusion criteria will be checked. Subjects will be familiarized with the floating tank. After this, the primary and secondary long-term outcomes will be assessed, as well as the expectancy/credibility rating.

At visits 2 - 6 (intervention), each separated by  $4 \pm 2$  days, in- and exclusion criteria will be checked again. Secondary short-term outcomes 1, 2 and 3 will be assessed. After this, a 5-minute ECG will be recorded for HRV analysis (short-term outcome 4). Subjects will then put on their bathing suits, take a shower and insert ear plugs before entering the floating tank (Tranquility, Floataway, Hingham, GB). The float itself will take 90 minutes. After the floating session subjects will leave the tank and take a shower to remove excess saline. Another 5-minute ECG will be recorded for HRV analysis (short-term outcome 4), before short-term outcomes 5 and 6 will be assessed.

After the last intervention, the subject is provided with a sealed envelope containing the questionnaires for the assessment of primary and secondary long-term outcomes and discharged.

On day 7 after visit no. 6 the subject is called by telephone and asked to fill out all questionnaires in the envelope and return it by mail.

This will be repeated at 12 weeks and 24 weeks after visit no. 6. Subjects in the intervention and control group will be unblinded after receipt of the last questionnaires.

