## Data analysis

All statistical analyses will be conducted using R (<https://www.r-project.org/>) and Python (<https://www.python.org/>). Pain and sensation drawings will be analysed with the FMRIB Software Library (<https://fsl.fmrib.ox.ac.uk/fsl/>).

The statistical test for the primary outcome will be a two-tailed two-sample t-test of the differences (before treatment - one week after treatment). In case of significant differences in the primary outcome measure at baseline, an ANCOVA model will be used instead. If the prerequisites for t-tests are not granted, we will use non-parametric tests to compare the differences. The study will be positive if we observe a significant difference ( $p < 0.05$ ) between the intervention and the control group.

For the secondary long-term outcomes we will use Chi-squared test (for the dichotomous condition) and mixed ANOVAs with between-subject factor "group" and within-subject factor "time" for the other outcomes. Secondary short-term outcomes will be assessed using two-tailed paired t-tests.

All outcomes will be assessed in an Intention-to-Treat (ITT) analysis under the following conditions:

- The subjects who drop out before the first session will be excluded from the analysis and replaced by other subjects.
- We will continue to acquire the endpoints, keeping the same time intervals, i.e. 1, 12 and 24 weeks after the last session.
- In the case that we cannot assess the endpoint due to missing data, the subject will be excluded from the analysis and replaced by another subject.

In order to test for the robustness of the therapeutic effect, we will also conduct per-protocol analyses afterwards.

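### Pain area and widespreadness are implied to be a one-week long-term endpoint but listed only as an acute short-term one, and as written neither classification can be analysed as planned

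*Combined protocol and SAP*

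**What the plan says.** Five places in the combined protocol and SAP bear on this endpoint.

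- **Endpoints.** Short-term endpoints are to be taken on both sides of each float. Of the long-term endpoints it says that "the latter will be assessed one week after the final floating session and in two follow-ups at 12 and 24 weeks after completion". It then adds: "The only exception are pain area and widespreadness that will not be included in the follow-up assessments".
- **Outcome lists (under Primary outcome).** Pain area and widespreadness are not among the seven secondary long-term outcomes. They appear once, as short-term outcome 2: "Acute pain area and widespreadness (from electronic pain drawing".
- **Study assessments, item 3.** Pain area and the widespread pain index (WPI) "will be derived from electronic pain drawings acquired using the tablet PC application" named there. The recall is then set: "Ratings will assess the period of four weeks before the day of assessment". The other pain ratings and the questionnaires (items 1 and 2) use one week.
- **Study procedures on each study day.** Visit 1 takes the primary and secondary long-term outcomes. At visits 2 to 6, short-term outcomes 1, 2 and 3 are listed before the float; after it come a second ECG and outcomes 5 and 6. After the last float "the subject is provided with a sealed envelope containing the questionnaires for the assessment of primary and secondary long-term outcomes and discharged". On day 7 the patient is telephoned and "asked to fill out all questionnaires in the envelope and return it by mail".
- **Data analysis.** Non-dichotomous secondary long-term outcomes get a mixed ANOVA with group and time as factors. For the rest: "Secondary short-term outcomes will be assessed using two-tailed paired t-tests".

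**The concern.** The classification of this endpoint decides when it is measured, how it is collected and which test is used. The plan gives two classifications, and the procedures fully support neither.

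At stake is whether the spatial spread of pain can be compared between real and placebo floating. The Rationale calls patient blinding crucial because large placebo effects are expected, and a within-patient change cannot separate floating from a placebo response. Leaving the classification open also means that the time point and the test could be settled after the data are seen.

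**Working it through.** The plan gives no figure for this endpoint, so there is none to reproduce. The check compares the sections and then works out what a four-week recall covers.

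**Step 1. Which classification does Endpoints imply?** An exception must belong to the class it is excepted from. The sentence follows the long-term schedule, and only weeks 12 and 24 are called follow-ups there. The natural reading is therefore a long-term endpoint measured at one week only. If it meant a short-term outcome that is simply not followed up, it could not be the only exception, because no short-term outcome is followed up.

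**Step 2. Follow each classification through.**

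| | If long-term (Endpoints) | If short-term (outcome list) |
|---|---|---|
| Baseline | Visit 1, in person; a tablet drawing is feasible | Before the float at each of visits 2 to 6 |
| Later value | One week: mailed questionnaires; no tablet, visit or paper chart described | After the float: outcome 2 not listed |
| Test | Mixed ANOVA with a group factor | Paired t-test, no group factor |
| What is lacking | A means of collecting the one-week drawing | The second half of the pair, and any comparison of arms |

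**Step 3. Recall against timing.** Inputs: a recall of 4 × 7 = 28 days (Study assessments); float visits 4 ± 2 days apart, so 2 to 6 days per gap, and the one-week assessment on day 7 after visit 6 (both Study procedures). Treatment is taken to start at visit 2.

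- Gaps from visit 2 to visit 6: 4. Nominal span 4 × 4 = 16 days; shortest 4 × 2 = 8; longest 4 × 6 = 24.
- Pre-treatment days in the one-week window = max(0, 28 − (span + 7)). Nominal 28 − 23 = 5; shortest course 28 − 15 = 13; longest course 28 − 31 < 0, so 0.
- Pre-treatment days in a visit-6 pre-float window = 28 − span. Nominal 28 − 16 = 12 (43%); longest course 28 − 24 = 4 (14%); shortest course 28 − 8 = 20 (71%).
- Two drawings around one 90-minute float: the float is 1.5 of 28 × 24 = 672 hours, about 0.2% of the window. The two ratings would describe almost the same four weeks.

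So the four-week recall does not fit an acute measure, and it dilutes a post-course one.

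**Step 4. Would a one-week recall remove the dilution?** A 7-day window ending on day 7 after visit 6 begins at visit 6, so it holds no pre-treatment days. A 7-day window ending at visit 6 also begins after visit 2, because the shortest span is 8 days.

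**The case against.** The best reply is that Endpoints never states a one-week measurement. Apart from one loosely worded sentence, the outcome list, the instrument and the procedures are consistent with a tablet drawing taken at float visits and left out of the mailings. On that view no one-week value was promised and none is missing. It stands that the one-week value is implied and not stated. But this reading does not explain why these measures are the only exception, and it does not explain the four-week recall.

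A second reply is that Endpoints says in general that short-term outcomes are taken on both sides of each float, so a post-float drawing may be intended. That is possible; outcomes 1 and 3 are likewise missing from the post-float list. Even then, the two windows would be nearly identical and the paired test would still not compare arms.

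A reader might also infer stronger statements that the documents do not support:

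- *That none of the 75 patients would have a visit-1 drawing and that all data for the mixed ANOVA would be missing.* The first assumes the short-term classification and the second the long-term one. If the endpoint is long-term, visit 1 already calls for it.
- *That the mailed assessment cannot collect the drawing.* The documents only describe no means of doing so.
- *That there is no between-group test at all.* This holds only under the short-term classification.
- *That the missing drawings in the 25 no-treatment patients are a fault of this endpoint.* No visit schedule is given for that group, which affects every short-term outcome and is a broader matter.

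**Conclusion.** The inconsistency is real and leaves one secondary endpoint without a workable analysis. Read as long-term, it has a planned group comparison but no described way of obtaining the one-week value. Read as short-term, it has no scheduled post-float drawing for its paired test, and that test does not compare arms. The four-week recall fits neither use well: about 5 of 28 days (range 0 to 13) in the one-week window would precede treatment.

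This rests on reading the exception sentence as implying a one-week value and on taking the procedures as written; unwritten practice may differ. The day counts assume that every visit gap lies within 4 ± 2 days. The primary outcome, the success criterion and the seven listed secondary long-term outcomes are untouched. This should be corrected, but it does not threaten the trial's main conclusion.

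**What to change.** Use one definition in Endpoints, the outcome lists, Study assessments, Study procedures and Data analysis.

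**Preferred.**

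- List pain area and WPI as secondary long-term outcomes, assessed at visit 1 and one week after the last float only.
- Take the visit-1 drawing on the tablet, and put a body chart on the same template in the one-week envelope.
- Use a one-week recall at both time points, matching the other ratings.
- Analyse between groups with the other secondary long-term outcomes, using either the planned group-by-time model or a comparison adjusted for the visit-1 value.

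The cost is wording, one drawing at an existing visit and one chart in an existing mailing. The drawbacks are a change from tablet to paper, which is the same in all arms, and the work of digitising the charts. Including the no-treatment group also requires a one-week date for it, since the present date is counted from visit 6.

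**Otherwise.** Delete the exception sentence, make no one-week claim, and compare intervention with control on the visit-6 pre-float drawing, adjusted for the visit-2 pre-float drawing. This needs no new assessments. State that it follows only four floats and excludes the no-treatment group. With a four-week recall, about 12 of the 28 days (range 4 to 20) precede treatment, so shorten the recall or acknowledge the dilution.

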### Primary outcome (long-term):

The primary endpoint of the study is the reduction of pain (maximum and average) as measured by a numeric rating scale (NRS) retrospectively for one week.

**Secondary long-term outcomes** comprise improvements in

- 1.) Reduction of pain (maximum and average) by 30% or more (dichotomous)
- 2.) Pain-related disability (PDI)
- 3.) Trait Anxiety (STAI Trait)
- 4.) Depression (BDI)
- 5.) Quality of life (SF-12)
- 6.) Quality of sleep (NRS)
- 7.) Use of pain medication

**Secondary short-term outcomes** comprise improvements in

- 1.) Acute pain intensity (NRS)
- 2.) Acute pain area and widespreadness (from electronic pain drawing)
- 3.) State Anxiety (STAI State)
- 4.) Heart rate variability (improvement of sympatho-vagal balance indicated by an increase in HF- and a decrease in LF-HRV)
- 5.) Unusual bodily sensations during floating (electronic drawing)
- 6.) Altered states of consciousness during floating (5D-ASC)

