## Study population / Sample size calculation

Sample size calculation is based on a previous explorative studie [5] that showed significant differences between a treatment and a no-treatment group:

|             | Treatment (20) | No-treatment (17) |
|-------------|----------------|-------------------|
| Pain before | 61.75 ± 18.78  | 59.06 ± 17.68     |
| Pain after  | 37.25 ± 30.22  | 60.41 ± 17.21     |

With this number we compute the difference post-pre, which yields  $-24.50 \pm 35.58$  for the treatment group and  $1.35 \pm 24.67$  for the no-treatment group. These differences give a Cohen's d-value of 0.83.

For a two-tailed, two-sample t-test, it means that we need a sample size of 24 subjects per group ( $\alpha=0.05$ ,  $1-\beta=0.95$ , allocation ratio 1:1). To account for attrition we will recruit 25 patients per group, i.e. 75 in total. Drop-outs will be replaced should the size of any group drop below 24 patients.

Groups will be balanced for age, gender and average pain intensity (retrospective NRS rating of the last week), and subjects will be recruited according to the following criteria.

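### Two pain scores are primary under one unadjusted p < 0.05 rule, and the plan does not say how they decide success together

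*Combined protocol and SAP*

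**What the plan says.** Under Endpoints, the primary outcome paragraph reads: "The primary endpoint of the study is the reduction of pain (maximum and average", rated on an NRS over the preceding week. Maximum and average pain are two ratings, each with its own change score.

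Success is defined twice. Endpoints says: "The study is successful, when the primary outcome shows significant differences between the intervention group and the control group at first assessment", meaning one week after the last session. Data analysis says: "The statistical test for the primary outcome will be a two-tailed two-sample t-test of the differences", and then "The study will be positive if we observe a significant difference" with p < 0.05 between intervention and control.

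The sample-size section uses a single score labelled only as pain: "These differences give a Cohen's d-value of 0.83", two-tailed alpha 0.05, power 0.95, "allocation ratio 1:1", and concludes "we need a sample size of 24 subjects per group". Recruitment is set slightly higher: "To account for attrition we will recruit 25 patients per group, i.e. 75 in total". Groups are balanced on average pain, not maximum pain.

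The first secondary long-term outcome, a reduction of at least 30%, again names both scores. The switch to ANCOVA depends on a baseline difference in a primary measure written in the singular. The cover page says that the SAP is contained in the protocol and that the protocol was not altered after approval, so no separate SAP or amendment is listed that could settle the matter.

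**The concern.** A confirmatory rule must give one answer for any set of results. Suppose average pain gives p = 0.03 and maximum pain gives p = 0.12. The plan does not say whether that trial is positive. There is no hierarchy, no division of alpha and no co-primary statement.

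Two things are at stake. First, the 5% error rate: it is not protected if one significant score out of two is enough, or if the team settles on a score once the results are known. Second, power: the calculation covers one test, so a rule requiring both scores has less power than that calculation implies.

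The same gap reaches two other places. The 30% responder is not uniquely defined. It is also unclear which score's baseline difference triggers ANCOVA, or whether both analyses then change.

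**Working it through.** **Inputs from the plan.** Two-tailed alpha 0.05, power 0.95, 1:1 allocation, d = 0.83, 24 per group (sample-size section); two-sample t-test on change scores, p < 0.05 (Data analysis).

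**Assumed, because the plan does not give it.** The correlation r between the two test statistics, taken as 0.5 to 0.9, with 0 and 0.95 as wider limits. For power, d = 0.83 on both scores.

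**Step 1: the plan's own figure.**
- SDs of change: √(18.78² + 30.22²) = 35.58 and √(17.68² + 17.21²) = 24.67. Both reproduce.
- Pooled SD: √[(19 × 35.58² + 16 × 24.67²)/35] = 31.07, so d = (24.50 + 1.35)/31.07 = 0.83. This reproduces.
- n per group at 95% power: 2(1.960 + 1.645)²/0.83² = 37.7, so 38; the exact t-test solution is 38.7, so 39. The stated 24 does not reproduce.
- n per group at 80% power: 2(1.960 + 0.842)²/0.83² = 22.8, so 23; the exact t-test solution is 23.8, so 24. Exact power at n = 24 is 80.4%.

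The power shortfall is a separate matter, but it fixes the base for the joint-power figures, so both bases are shown.

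**Step 2: false-positive rate, no effect on either score.** With (Z₁, Z₂) bivariate normal:
- either suffices: 1 − P(|Z₁| ≤ 1.96 and |Z₂| ≤ 1.96); at r = 0 this is 1 − 0.95² = 0.0975;
- both required: 0.05 + 0.05 − P(either).

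**Step 3: power when both are required.** Φ₂(z, z; r), with z = 1.645 for 95% per test and z = 0.842 for 80% per test.

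| r | Error, either suffices | Error, both required | Joint power, 95% each | Joint power, 80% each |
|---|---|---|---|---|
| 0 | 9.75% | 0.25% | 90.3% | 64.0% |
| 0.5 | 9.1% | 0.9% | 91.2% | 68.7% |
| 0.7 | 8.4% | 1.7% | 92.0% | 71.3% |
| 0.8 | 7.8% | 2.2% | 92.5% | 72.9% |
| 0.9 | 7.0% | 3.0% | 93.2% | 75.0% |
| 0.95 | 6.5% | 3.5% | 93.7% | 76.5% |

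If only one score has a true effect, the both-required rule still cannot exceed 5%, because the null score must itself pass at 0.05.

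**Step 4: check with t-tests.** Simulation at 24 per group (200,000 replicates) gives 9.0%, 8.4%, 7.8% and 7.2% for either-suffices at r = 0.5, 0.7, 0.8 and 0.9. Joint power runs from 69.1% (r = 0.5) to 75.2% (r = 0.9). This agrees with the table.

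**Step 5: cost of dividing alpha.** At alpha 0.025 and n = 24, exact power per measure is 71.1%. Restoring 80% needs 28.9, so 29 per group.

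**The case against.** A reader might infer that the plan lets the trial succeed on either score, so that its error rate exceeds 5%. The documents do not say so. The two scores are joined by a conjunction, the Endpoints section speaks of differences in the plural, and the Data analysis section describes one test of one primary outcome. A both-required rule, or a composite fixed in advance, fits that wording at least as well as an either-suffices rule. Under the first the error rate is at most 5%; under the second it is 5%. This objection stands: the inflation is conditional.

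It would also be wrong to say that every two-measure reading breaks the stated error rates. Under a both-required rule alpha is respected and only power suffers. Nor does the plan claim 80% power. It claims 95%, and the 80% is what its own n and d deliver on recalculation.

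One might answer that average pain is evidently the intended primary, since the groups are balanced on it. Balancing on a score does not make it the primary endpoint, and the endpoint definition names both.

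Finally, two ratings of the same week's pain are probably highly correlated, which would put the inflation nearer 7% than 9%. That is reasonable, but the documents give no correlation, and the rate stays above 5% for any r below 1. None of these replies supplies the missing rule.

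**Conclusion.** The concern holds as a missing decision rule: two primary scores, one unadjusted threshold, and no statement of how the scores combine. That much rests on the text alone.

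The size depends on the reading. If either score suffices, or the choice follows the data, the false-positive rate is about 9.1% to 7.0%, given the assumed correlation of 0.5 to 0.9. If both are required, error is controlled and the loss is in power. From the stated 95% per test, joint power is about 91% to 93%. From the roughly 80% that n = 24 gives, it is about 69% to 75%. Both ranges assume d = 0.83 on each score. The documents do not establish which reading was meant, so they do not support a flat statement that the trial's error rate exceeds 5%. Because the gap decides whether the trial is called positive, it must be closed.

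**What to change.** Before any outcome data are seen, name one score as the single primary at the one-week assessment. Average pain over the last week is the natural choice because the groups are already balanced on it, although another score named in advance would control error equally well. Test maximum pain second, at 0.05, only if average pain is significant. This fixed sequence holds 5% across the two tests, needs no extra patients and leaves the power of the first test unchanged. Define the 30% responder outcome and the baseline-difference check on the same score.

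The cost is that maximum pain can be claimed only after average pain succeeds. Since the SAP is part of the protocol, the change also needs an amendment presented to the ethics committee, as the Amendments section requires. Made after the results are known, the choice of score would give no protection.

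If both scores must remain primary with either allowed to succeed, Holm is valid but costs power. The smaller p-value must clear 0.025, where power per measure at n = 24 is about 71%, and 29 per group would be needed to restore 80%. If both are to be required, say so and redo the sample size for joint power.
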